## Abstract

Central retinal artery occlusion (CRAO; retinal stroke or eye stroke) is an under-recognized, disabling form of acute ischemic stroke which causes severe visual loss in one eye. The classical risk factor for CRAO is ipsilateral carotid stenosis; however, nearly half of patients with CRAO do not have high-grade carotid stenosis, suggesting that other cardiovascular risk factors may exist for CRAO. Specifically, prior studies have suggested that cardioembolism, driven by underlying atrial fibrillation, may predispose patients to CRAO. We describe the design of an observational, population-based study in this protocol. We evaluate two specific objectives: 1) To determine if atrial fibrillation is an independent risk factor for CRAO after adjusting for medical and cardiovascular risk; 2) To determine if use of oral anticoagulation can modify the risk of CRAO for patients with atrial fibrillation. This protocol lays out our strategy for cohort definition, case and control definition, comorbidity ascertainment, and statistical methods.

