### Biological rationale

The prevailing paradigm is that CRAO arises because of ipsilateral stenotic carotid plaque [3] releasing predominantly calcium or cholesterol emboli. However, this observation is drawn from studies evaluating patients with branch retinal arterial occlusion (BRAO) where emboli may be visualized on funduscopic examination [4]. This may have falsely increased the perceived contribution of calcium/cholesterol emboli to CRAO as these emboli are less likely to autolyze when compared with fibrin-based emboli and are thus visible longer. Recently, we demonstrated that tissue plasminogen activator (tPA, a drug that breaks up fibrin-based clots) improved the rate of visual recovery in some patients with CRAO, providing evidence against the assertion that CRAO is caused exclusively by cholesterol or calcium emboli [5–7]. Furthermore, over 50% of people with CRAO do not have high-grade ipsilateral carotid stenosis [8] and 30% of people with CRAO do not have even mild ipsilateral carotid disease [9].

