### Prior work addressing this question

There is a higher burden of AF in people with CRAO than in the general population. One prior insurance-based cohort study in Taiwan described a higher incidence of CRAO in patients with AF than in the general population [10]. This study adjusted for age, sex and year of presentation but did not adjust for vascular risk factors or medication exposures. Additionally, other studies have reported a higher prevalence of AF in patients with CRAO [11, 12] than in the general population which lends credence to the hypothesis that the two conditions are associated. However, CRAO (like cerebral stroke) is a surrogate marker for vascular risk [8] so studies that comprehensively address this confounding are needed. We performed a study using healthcare cost and utilization project (HCUP) data from New York, California, and Florida hospitalizations and emergency department visits found that there was an inverse relationship between AF and CRAO [13]. However, this study lacked access to outpatient and prescription drug information, which resulted in systematic under-ascertainment of both AF and CRAO. Furthermore, this study could not evaluate whether exposure to anticoagulation in patients with AF could prevent the development of CRAO. Therefore, a study using inpatient, outpatient, and pharmacy claims data would be essential to definitively determine whether cardioembolism is a potential causative etiology for CRAO, and whether anticoagulation can modify this risk factor. That only 50–60% of people meeting guideline criteria for anticoagulation for AF are actually treated with an anticoagulant creates an intriguing opportunity to leverage real-world data to conduct a quasi-randomized study to examine the interplay between anticoagulation and CRAO risk [14].

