### Inclusion and exclusion criteria (Aim 2)

Inclusion criteria are fee-for-service Medicare enrollment for at least 12 consecutive month and 12 months FFS with Part A, B, and D enrollment following the index date for at least 12 months or until death, and presence of atrial fibrillation as defined in the exposure section. The index date for patients exposed to anticoagulation will be the date of the first anticoagulant prescription drug claim occurring after the diagnosis of AF. For potential controls, only patients with no exposure to anticoagulation throughout the study period would be eligible to avoid selecting controls who start an anticoagulant during the follow-up period. For controls, inclusion and exclusion criteria will be examined for each year after AF diagnosis, and the midpoint of one random year will be selected as the index date for each control patient.

Exclusion criteria include:

Patients with any claim for CRAO in the 12 months prior to AF diagnosis or index date for controls;Patients who die within first 12 months of enrollment;Patients taking therapeutic-dose heparin, enoxaparin, dalteparin, fondaparinux, or betrixaban.

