### Adjustment covariates

We will utilize the following pre-specified covariates for risk adjustment: age, biological sex, race/ethnicity, and cardiovascular comorbidities and medical risk factors, including the medical comorbidities included in the Charlson Comorbidity Index (except for cardiac arrhythmias, which subsumes our primary exposure of interest), and additionally including hypertension, hyperlipidemia, valvular heart disease, and smoking status, using validated ICD-9-CM and ICD-10-CM algorithms [20–23]. Carotid stenosis and Stroke/TIA are contained in the cerebrovascular disease group of the Charlson Comorbidity Index. S1 and S2 Figs show the directional acyclic graphs representing our understanding of possible confounding variables.

We will ascertain comorbidities using a twelve-month look-back period from the patient’s index date (July 1 of initial year of inclusion in cohort for controls) using established claims-based algorithms. These are outlined in Table 2, below.

**Table 2 pone.0296251.t002:** List of international classification of diseases codes used for comorbidity adjustment.

Comorbidity	ICD-9 Code	ICD-10 Code	Citation
Hypertension	401.*, 402.*, 403.*, 404.*, 405.*, 437.2*	I10.*-I13.*, I15.0, I15.2, I15.8, I15.9, I16.*, I67.4*	Birman-Deych, 2005 [21]
Hyperlipidemia†	272.x	E78.x	Oake, 2017 [22]
Tobacco Use††	305.1, 649.0x, 989.84, V15.82; CPT codes 99406, 99407, G0436, G0437, G9016, S9453, S4995, G9276, G9458, 1034 F 4004 F 4001 F	F17.x, T65.2xx, Z87.891, CPT codes 99406, 99407, G0436, G0437, G9016, S9453, S4995, G9276, G9458, 1034 F 4004 F 4001 F	Desai, 2016 [23]
Valvular Heart Disease	394.*, 395.*, 396.*, 397.*, 398.9*, V42.2*, V43.3*, 424.*	I05.*-I08.*, I09.1*, I09.81, I09.89, I09.9*, I34.*-I39.*, Z95.2*, Z95.3*, Z95.4*	Birman-Deych, 2005 [21]

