Paraplegia and Hemiplegia	334.1*, 342.*, 343.*, 344.0*, 344.1*, 344.2*, 344.3*, 344.4*, 344.5*, 344.6*, 344.9*	G04.1*, G11.4*, G80.*-G82.*, G83.0*-G83.4*, G83.9*	Quan, 2005 [20]
Renal Disease	403.01, 403.11, 403.91, 404.02, 404.03, 404.12, 404.13, 404.92, 404.93, 582.*, 583.0*, 583.1*, 583.2*, 583.4*, 583.6*, 583.7*, 585.*, 586*, 588.0*, V42.0*, V45.1*, V56.*	I12.0, I13.11, I13.2*, N03.*, N05.2*-N05.5*, N05.9*, N06.2*-N06.5*, N07.2*-N07.5*, N08.*, N17.1*, N17.2*, N18.*, N19.*, N25.0*, Z48.22, Z49.0*, Z49.3*, Z94.0*, Z99.2, Z91.15	Quan, 2005 [20]
Non-metastatic cancer	140.*, 141.*, 142.*, 143.*, 144.*, 145.*, 146.*, 147.*, 148.*, 149.*, 150.*, 151.*, 152.*, 153.*, 154.*, 155.*, 156.*, 157.*, 158.*, 159.*, 160.*, 161.*, 162.*, 163.*, 164.*, 165.*, 170.*, 171.*, 172.*, 174.*, 175.*, 176.*, 179*, 180.*, 181*, 182.*, 183.*, 184.*, 185*, 186.*, 187.*, 188.*, 189.*, 190.*, 191.*, 192.*, 193*, 194.*, 195.*, 200.*, 201.*, 202.*, 203.*, 204.*, 205.*, 206.*, 207.*, 208.*, 238.6*	C00.*-C26.*, C30.*-C34.*, C37.*-C41.*, C43.*, C45.0*-C45.2*, C45.7*, C45.9, C46.*-C58.*, C60.*, C61.*, C62.0*, C62.1*, C62.9*, C63.*-C76.*, C81.*-C86.*, C88.2*-C88.4*, C88.8*, C88.9*, C90.*-C93.*, C94.0*, C94.1*, C94.2*, C94.3*, C94.8*, C95.*, C96.0*, C96.2*, C96.4*, C96.9*, C96.A, C96.Z, D03.*, D45.*, D47.Z9	Quan, 2005 [20]
Moderate to severe liver disease	456.0*, 456.1*, 456.2*, 572.2*, 572.3*, 572.4*, 572.8*	I85.*, K70.41, K71.11, K72.01, K72.1*, K72.9*, K76.6*, K76.7*	Quan, 2005 [20]
Metastatic cancer	196.*, 197.*, 198.*, 199.*	C77.*-C80.*	Quan, 2005 [20]
HIV/AIDS	042*, 043*, 044*	B20.*	Quan, 2005 [20]
Depression	296.2*, 296.3*, 296.5*, 300.4*, 309.*, 311*	F31.3*-F31.5*, F31.75, F31.76, F32.*, F33.*, F34.1*, F43.10, F43.11, F43.12, F43.2*, F43.8*, F43.9*, F93.0*, F94.8*);	Quan, 2005 [20]
Drug abuse	292.*, 304.*, 305.2*, 305.3*, 305.4*, 305.5*, 305.6*, 305.7*, 305.8*, 305.9*, V65.42	F11.*-F16.*, F18.*, F19.*, Z71.41, Z71.6, Z71.51	Quan, 2005 [20]
Psychoses	293.8*, 295.*, 296.04, 296.14, 296.44, 296.54, 297.*, 298.*	F06.*, F20.*, F22.*-F25.*, F28.*, F29.*, F30.2*, F31.2*, F31.5*, F32.3*, F33.3*, F44.89, F53.*	Quan, 2005 [20]

^†^Claims data do not sensitively identify patients with hyperlipidemia. One prior validation study showed that this code was 32% sensitive/100% specific for hyperlipidemia [22].

^††^Claims data do not sensitively identify tobacco use, though are highly specific [23].

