#### Descriptive analysis

Using the weighted analytic cohort, we will calculate means with standard deviations and medians with interquartile ranges to summarize the distribution of continuous, normally distributed variables, and medians with interquartile ranges to summarize the distribution of continuous, not normally distributed variables. We will summarize categorical data using counts with percentages. Data will be stratified by presence of atrial fibrillation and include key demographic and clinical factors. For Aim 2, we will additionally summarize anticoagulant usage patterns among patients with atrial fibrillation, including class of agent utilized (DOAC vs. warfarin), number of monthly fills per calendar year, and duration of exposure in months. Table shells are provided in Tables 3–5.

**Table 3 pone.0296251.t003:** Characteristics of the overlap-weighted primary analysis cohort defined at first date of meeting study eligibility.

Characteristic	Total Sample (N = xxxx)	Patients with AF (n = xxxx)	Patients without AF (n = xxxx)	Standardized Difference
Age, mean (SD)				
Women, n (%)				
Race/ethnicity, n(%)				
Asian/Pacific Islander				
Black, non-Hispanic				
Hispanic				
White, non-Hispanic				
Comorbidities (n, %)				
Cerebrovascular Disease				
Chronic Kidney Disease				
Congestive Heart Failure				
Coronary Artery Disease				
Diabetes Mellitus				
Hyperlipidemia				
Hypertension				
Peripheral Vascular Disease				
Smoking				

**Table 4 pone.0296251.t004:** Characteristics of the secondary analysis (Part-D enrolled) cohort defined at first date of meeting study eligibility.

Characteristic	Total Sample (N = xxxx)	Patients with at least one fill for anticoagulant (n = xxxx)	Patients without any anticoagulant use (n = xxxx)	Standardized Difference
Age, mean (SD)				
Women, n (%)				
Race/ethnicity, n(%)				
Asian/Pacific Islander				
Black, non-Hispanic				
Hispanic				
White, non-Hispanic				
Comorbidities (n, %)				
Cerebrovascular Disease				
Chronic Kidney Disease				
Congestive Heart Failure				
Coronary Artery Disease				
Diabetes Mellitus				
Hyperlipidemia				
Hypertension				
Peripheral Vascular Disease				
Smoking				
Antiplatelet agent use				
Oral anticoagulant use				
Lipid-lowering agent				
Oral hypoglycemic agent				
Oral antihypertensive agent				

**Table 5 pone.0296251.t005:** Anticoagulation usage patterns among patients with atrial fibrillation with at least one Part D fill for an anticoagulant medication.

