#### Regression modeling (aim 2)

a) In keeping with target trial emulation methodology as described above, the index date for patients exposed to anticoagulation will be the date of the first anticoagulant prescription drug claim occurring after the diagnosis of AF. For potential controls, only patients with no exposure to anticoagulation throughout the study period would be eligible to avoid selecting controls who start an anticoagulant during the follow-up period. For controls, inclusion and exclusion criteria will be examined for each year after AF diagnosis, and the midpoint of one random year will be selected as the index date for each control patient.b) Similar to Aim 1, patients diagnosed with CRAO precedent to or concurrent to AF diagnosis will be excluded and these patients will be examined in an exploratory analysis.c) Our primary analysis will utilize propensity score overlap weighting methodology to approximate a randomized design where baseline hazard of CRAO of patients receiving anticoagulation vs. not receiving is comparable. We will incorporate the following variables to define the propensity score: age, time since first AF claim, sex, geography, race, Medicaid dual eligibility, vascular comorbidities and non-vascular comorbidities relevant to the likelihood that a patient will be treated with anticoagulation (to include all of the comorbidity variables included for Aim 1 propensity score, as well as history of gastrointestinal bleeding or peptic ulcer disease (using validated ICD-9-CM codes 531.x (gastric ulcer), 532.x (duodenal ulcer), and 578.x (gastrointestinal hemorrhage) and their ICD-10-CM counterparts K25.x, K26.x, and K92.2) and history of intracranial hemorrhage (any of ICD-10-CM I60, I61, S06.3, S06.4, S06.5, S06.6 and their ICD-9-CM counterparts 430.x, 431.x, 432.x)) [32–35].d) Our principal effect of interest is the hazard of CRAO among patients treated with any oral anticoagulant agent compared to those not treated. Given variable patient adherence to anticoagulation, we will take advantage of the strength of Part D data (which records pharmaceutical fills rather than prescriptions) and treat anticoagulation exposure as a time-varying covariate for patients exposed to anticoagulation.e) We will perform identical sensitivity analyses as described in Aim 1.f) Table shells for the results of Aim 2 are shown in Table 8.

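### Both propensity scores control carotid stenosis only through a pooled cerebrovascular flag, and the Aim 2 score has no baseline drug term and no anticoagulant-free look-back

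*Protocol article*

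**What the plan says.** **Carotid stenosis.** The Abstract states: "The classical risk factor for CRAO is ipsilateral carotid stenosis". The Biological rationale adds that "over 50% of people with CRAO do not have high-grade ipsilateral carotid stenosis", which leaves a possibly large minority who do. Under Adjustment covariates, "Carotid stenosis and Stroke/TIA are contained in the cerebrovascular disease group of the Charlson Comorbidity Index". In Table 2 that group is a single row (ICD-9 430* to 438.*, with ICD-10 counterparts) covering hemorrhage, ischemic stroke, TIA and carotid disease. There is no carotid row.

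The Aim 1 score is built from these covariates (Regression modeling (aim 1), item e). The Aim 2 score takes over all Aim 1 comorbidities and adds, among others, a separate intracranial hemorrhage history (Regression modeling (aim 2), item c). The section on re-estimating propensity scores says that overlap weighting will balance baseline covariates exactly. Tables 3 and 4 report cerebrovascular disease only as the pooled group.

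**Drugs in Aim 2.** Item c begins: "We will incorporate the following variables to define the propensity score: age, time since first AF claim, sex, geography, race, Medicaid dual eligibility". It goes on to comorbidities and bleeding history, and names no drug. Table 4, for the Part D cohort at first eligibility, has rows for "Antiplatelet agent use" and for lipid-lowering, oral hypoglycemic and oral antihypertensive agents. A Table 2 footnote concedes: "One prior validation study showed that this code was 32% sensitive/100% specific for hyperlipidemia". Under Prior work, an earlier cohort is faulted because it "did not adjust for vascular risk factors or medication exposures".

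**Part D enrollment.** The Aim 2 criteria require "Part A, B, and D enrollment following the index date". The index date of a treated patient is the first anticoagulant claim after AF diagnosis. No preceding period free of anticoagulant fills is stated.

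**The concern.** Aim 1 asks whether AF raises CRAO risk independently of other vascular risk factors, so the leading rival explanation needs close control. Overlap weights equalize the means of terms that are in the score. A pooled yes/no flag can be perfectly balanced while the mix behind it differs, for instance more embolic stroke in one group and more carotid disease in the other. The planned standardized differences would then look ideal, and nothing in Tables 3 or 4 would warn the reader.

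Aim 2 uses weighting to make the baseline hazard of CRAO comparable between treated and untreated patients. Antiplatelet and lipid-lowering use could relate both to the decision to anticoagulate and to vascular risk. The hyperlipidemia diagnosis in the score misses about two thirds of cases on the protocol's own figure (100% - 32% = 68%). Without required pre-index Part D coverage, some patients labelled as starting an anticoagulant may be continuing users. That sits poorly with the target trial emulation the protocol claims.

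**Working it through.** The plan gives no figure on this point to reproduce. The first step is a reading of the covariate lists; the second is an illustration of size with assumed inputs.

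**Step 1: what weighting balances.** Let p be the weighted prevalence of the cerebrovascular flag, equal in both groups. Let a and c be the shares of flagged patients who have carotid disease in the AF and control groups. Weighted carotid prevalence is then p × a against p × c. These are equal only if a = c, and nothing in the score enforces that directly. In Aim 2 the separate hemorrhage term removes one component from the mixture, but carotid disease stays pooled with ischemic stroke/TIA.

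**Step 2: carotid stenosis, Aim 1.** With Rc and Rs the CRAO rate ratios for carotid disease and for other flagged disease, the hazard ratio is multiplied by about

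B = [(1 - p) + p(a·Rc + (1 - a)·Rs)] / [(1 - p) + p(c·Rc + (1 - c)·Rs)].

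Every input is an assumption; the documents give none of them.

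- Mild: p = 0.15, a = 0.30, c = 0.45, Rc = 3, Rs = 1.5. B = 1.1425/1.17625 = 0.97.
- Middle: p = 0.15, a = 0.30, c = 0.50, Rs = 1. With Rc = 2, B = 1.045/1.075 = 0.97. With Rc = 5, B = 1.18/1.30 = 0.91. With Rc = 10, B = 1.405/1.675 = 0.84.
- Strong: p = 0.25, a = 0.20, c = 0.50, Rc = 5, Rs = 1. B = 1.20/1.50 = 0.80.
- Strong, but prior stroke also carries risk (Rs = 3): B = 1.60/1.75 = 0.91.
- Equal shares (a = c): B = 1.00.
- Middle with the shares exchanged between groups, Rc = 5: B = 1.30/1.18 = 1.10, so the direction reverses.

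A wider grid (p 0.10 to 0.25, a 0.25 to 0.35, c 0.45 to 0.60, Rc 2 to 10, Rs = 1) gives 0.665 to 0.990. Its lower end needs every input at its extreme: (1 + 0.0625 × 9)/(1 + 0.15 × 9) = 1.5625/2.35.

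**Step 3: drugs, Aim 2.** For one unbalanced binary factor, B = [1 + pT(R - 1)]/[1 + pU(R - 1)], where pT and pU are its prevalence in treated and untreated patients and R is its rate ratio for CRAO. Inputs are again assumed.

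- Antiplatelet use 20% against 40%: R = 0.8 gives 0.96/0.92 = 1.04; R = 1.5 gives 1.10/1.20 = 0.92.
- Antiplatelet use 20% against 45%: R = 0.6 gives 0.92/0.82 = 1.12; R = 2 gives 1.20/1.45 = 0.83.
- Lipid-lowering use 60% against 45%: R = 0.6 gives 0.76/0.82 = 0.93; R = 1.25 gives 1.15/1.1125 = 1.03.

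**Step 4: effect of the change.** Once a factor is its own term in the score, its weighted prevalence is equal in both groups and its B is 1.00.

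**The case against.** The strongest reply is that carotid stenosis is in the score. The protocol says so openly, uses a published composite, and refers to causal graphs (S1 and S2 Figs) that are not shown. Myocardial infarction, peripheral vascular disease, diabetes, hypertension, hyperlipidemia and smoking are scored too and should carry part of the same atherosclerotic risk, which the formula above ignores. This stands. A reader might infer that carotid stenosis is left out or uncontrolled, and the documents do not support that.

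A reader might also infer that the bias is known to run downward, because embolic stroke sets the flag in AF patients and carotid disease sets it in controls. That is plausible but appears nowhere in the documents. The 0.80 figure further requires that prior stroke carry no CRAO risk, while the protocol itself treats CRAO, like cerebral stroke, as a marker of vascular risk. The formula also allows no patient to have both carotid disease and stroke. For Aim 2, where everyone has AF, the documents give no reason to expect different carotid shares by treatment.

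On drugs, diabetes and hypertension are already scored by diagnosis, so the case for hypoglycemic and antihypertensive agents is weak. Time since first AF claim is scored and may partly absorb late-observed continuing users. The Aim 2 enrollment sentence is unclear, so the absence of a pre-index Part D requirement is the explicit reading, not a certain one. Residual confounding is acknowledged under Limitations.

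None of this answers the core point. A causal graph cannot make a pooled flag balance its components. The protocol has already edited this composite by removing transient retinal occlusion codes, and has given hemorrhage its own Aim 2 term, so separating carotid stenosis would be in keeping with its own practice.

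**Conclusion.** The point holds as one of coarse control. Both scores can yield a perfectly balanced cerebrovascular flag with carotid stenosis unbalanced behind it, and the planned tables would not reveal this. Size and direction cannot be derived from the documents. Under the assumed inputs the effect on the Aim 1 hazard ratio is roughly 0 to 20%; only extreme combinations go further, and equal carotid shares give none.

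For Aim 2, the omission of drug terms is plain from the text and at odds with the protocol's own criticism of earlier work. Antiplatelet and lipid-lowering use matter most. The main antiplatelet example shifts the hazard ratio by +4% to -8%, with no determined sign. A reader might infer from Table 4 that the study already holds these drugs for everyone at baseline. It may not, because Part D is explicitly required only after index. For the same reason a first observed fill may be a refill; the size of that effect was not estimated.

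**What to change.** **At no cost in data or patients.** Enter carotid stenosis (the carotid codes within 433.* and I65.*) as a term separate from ischemic stroke/TIA in both propensity scores and in the adjusted models. Separate hemorrhage in Aim 1 as well; Aim 2 already has it. Add carotid stenosis as a row in Tables 3 and 4. These codes already lie within the listed group.

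**At modest cost, Aim 2.** State a requirement of 12 months of Part D before index with no anticoagulant fill, and add at least baseline antiplatelet and lipid-lowering use to the score. The hypoglycemic and antihypertensive rows are optional. The oral anticoagulant row of Table 4 is the exposure itself and stays out. The look-back loses some patients and events. The documents do not allow that number to be estimated, and CRAO is rare, so it should be counted before the rule is fixed. Antiplatelets obtained without a prescription remain unmeasured and should be named as a limitation.

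### Aim 2 balances stroke and bleeding histories without their timing, although only treated patients start follow-up at a treatment decision, so comparable baseline hazards are not secured in the first months

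*Protocol article*

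**What the plan says.** The start of follow-up is set in Inclusion and exclusion criteria (Aim 2) and repeated in Regression modeling (aim 2), item a. The rule in the treated arm reads: "The index date for patients exposed to anticoagulation will be the date of the first anticoagulant prescription drug claim occurring after the diagnosis of AF". Controls must never have been exposed during the study, and their rule reads: "the midpoint of one random year will be selected as the index date for each control patient".

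The covariates are set in Adjustment covariates: "We will ascertain comorbidities using a twelve-month look-back period from the" index date. The same sentence anchors the look-back for controls at "July 1 of initial year of inclusion in cohort for controls". Stroke has no variable of its own: "Carotid stenosis and Stroke/TIA are contained in the cerebrovascular disease group of the Charlson Comorbidity Index". In Table 2 that group also holds hemorrhage (430 to 432), precerebral disease (433), other cerebrovascular disease (437) and late effects (438, I69).

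Regression modeling (aim 2), item c, adds "history of gastrointestinal bleeding or peptic ulcer disease" and a history of intracranial hemorrhage. It gives no look-back window specific to these two. The only timing variable listed for the score is time since first AF claim.

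The stated purpose of the weighting is "to approximate a randomized design where baseline hazard of CRAO of patients receiving anticoagulation vs. not receiving is comparable". The Limitations section counts the choice of index date and controls as a strength. It would also take a replicated stroke benefit and a replicated excess of intracranial hemorrhage as support for the CRAO result.

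**The concern.** Overlap weighting balances what is in the score and nothing else. Here one arm's time zero is a treatment decision, which a recent stroke or TIA can trigger and a recent bleed can postpone. The other arm's time zero is tied to no clinical event. Two arms can therefore have the same proportion with a cerebrovascular code while the events lie days before index in one arm and months before in the other. Vascular risk plausibly depends on that interval.

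The time-varying exposure does not remove this. Every treated patient is on drug at index by construction, so the first months compare recent initiators with controls directly.

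At stake are the early part of the CRAO comparison and, more so, the ischemic stroke and intracranial hemorrhage endpoints. Recent stroke and recent bleeding are the histories most likely to move those two outcomes, and those outcomes are the plan's own check on validity.

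**Working it through.** The plan gives no figure on this point. Its power calculation is for Aim 1 and does not bear on it. All numerical inputs below are assumptions.

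**Step 1. Can equal flags hide unequal timing?** A simulation of 200,000 patients used a 20% stroke flag and a 10% bleed flag, with event dates uniform over 12 months. The logistic score contained age, time since AF and the two flags. The log-odds of starting treatment were raised by 1 or 2 for a stroke in the last month, and lowered by the same amount for a bleed in the last month. After overlap weighting both flags balanced (standardized difference 0.00), but recency did not:

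| Log-odds for recency | Stroke in last month, treated vs control | Std. diff. | Bleed in last month, treated vs control | Std. diff. |
|---|---|---|---|---|
| 0 | 1.7% vs 1.7% | 0.00 | 0.8% vs 0.8% | 0.00 |
| 1 | 2.5% vs 1.0% | 0.11 | 0.4% vs 1.0% | -0.07 |
| 2 | 2.9% vs 0.45% | 0.19 | 0.2% vs 1.0% | -0.11 |

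The first row matters: if recency does not drive initiation, there is no imbalance. Table 4 as laid out has one cerebrovascular row and no bleeding row, so it could not show the difference.

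**Step 2. What could it do to the hazard ratio when the true value is 1?** Let *p* be the flagged share, equal in both arms after weighting. Let *s* be the share of flagged events in the last month before index. For controls, uniform timing gives s = 1/12 = 8.3%. With r and o the mean hazards over follow-up for recent and older events, relative to unflagged patients:

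- arm mean = (1 − p) + p[s·r + (1 − s)·o]
- hazard ratio ≈ treated mean / control mean

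Central inputs: p = 20%, treated s = 60%. The hazard is 5 in the first month after the event, 3 in months 2 to 3, 2 in months 4 to 12, and 1.4 after that.

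| Follow-up | r | o | Flagged, treated | Flagged, control | Arm means | Ratio |
|---|---|---|---|---|---|---|
| 1 month | 4.00 | 2.11 | 3.24 | 2.27 | 1.449 / 1.253 | 1.16 |
| 12 months | 2.267 | 1.690 | 2.036 | 1.738 | 1.207 / 1.148 | 1.05 |
| 36 months | 1.689 | 1.497 | 1.612 | 1.513 | 1.122 / 1.103 | 1.02 |

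Example for 12 months: treated flagged = 0.6 × 2.267 + 0.4 × 1.690 = 2.036. Control flagged = (1/12) × 2.267 + (11/12) × 1.690 = 1.738. The ratio is (0.8 + 0.2 × 2.036) / (0.8 + 0.2 × 1.738) = 1.05.

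**Step 3. Range.** The inputs were varied over p = 10 to 30%, s = 30 to 80%, a first-month hazard of 3 to 8, and a late hazard of 1.3 to 1.5. The ratio runs from 1.00 to 1.17 over one year and from 1.00 to 1.06 over three. The upper end depends on the intermediate hazard steps: two reasonable sets gave 1.14 and 1.17 at one year.

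**Step 4. A milder case.** With s = 20% and the other central inputs unchanged, 12 months gives 0.2 × 2.267 + 0.8 × 1.690 = 1.805. The ratio is then (0.8 + 0.2 × 1.805) / 1.148 = 1.01. Across the other ranges, s = 20% gives at most 1.03 over one year and 1.01 over three.

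**Step 5. Covariate date.** Adjustment covariates anchors the control look-back at July 1 of the initial year. The Aim 2 control index date is the midpoint of a random year after AF diagnosis. Read literally, a control's history could be measured at a date other than the start of follow-up. The two passages need to be reconciled before any recency term has a meaning.

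**The case against.** The strongest case against is that the effect is small and rests on assumption.

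- **Precision.** Patients are followed to death, disenrollment or 85% attrition, so the longer horizon counts most. Suppose 200 CRAO events split evenly between arms, which at the article's 22 per 100,000 per year needs about 200 / 0.00022 ≈ 909,000 person-years. The 95% interval is then the estimate divided or multiplied by exp(1.96 × √(4/200)) = 1.32. A shift of 2 to 5% would not change a CRAO conclusion. This stands, and it limits the weight of the point.
- **The flag is broad.** Carotid disease and late-effect codes are not dated acute events that prompt a fill, so a high recent share cannot apply to all of them. This stands too: Step 4 shows how quickly the effect shrinks.
- **Time since first AF claim is in the score.** Where a stroke reveals AF and prompts treatment, this term may absorb part of the imbalance. The calculation gives it no credit. It also compares arm means and does not fit the planned time-varying model.
- **Level of detail.** Coding of covariates is often left to an analysis plan. But the article itself fixes the index dates, code lists, general window and score contents, and states the comparability it aims for. The point concerns those choices.
- **Residual confounding is acknowledged.** The acknowledgement is general, and this source can be measured in claims already held.

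A reader might infer that the baseline hazards are in fact unequal, that the result is biased against anticoagulation, or that the known hemorrhage harm will be hidden. The documents do not support this. They do not say how often strokes prompt or bleeds delay a fill. Yes/no coding is inferred from the code lists and the n (%) table shells. The 12-month window is stated for comorbidities in general and not separately for the bleeding histories. No calculation was made for hemorrhage.

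**Conclusion.** The point holds in limited form. The index dates differ in kind between arms, and the score has no term for time since a stroke, TIA or bleed. Balance on the listed variables therefore does not secure the comparable baseline hazard that item c aims for. The exposure is mainly in the first months after index, and for the stroke and intracranial hemorrhage endpoints used to judge validity.

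With a true hazard ratio of 1, the assumed inputs give about 1.16 in the first month, 1.05 over one year and 1.02 over three in the central case. The ranges are 1.00 to 1.17 and 1.00 to 1.06 at one and three years. These are upward shifts only if recent strokes prompt fills. They shrink if many flags are chronic codes or if AF duration tracks stroke recency. For hemorrhage, neither size nor direction is established. This is a worthwhile, cheap improvement. It is not a flaw that invalidates Aim 2.

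**What to change.** In the Aim 2 propensity score:

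- Take acute ischemic stroke/TIA out of the cerebrovascular group and give it its own variable.
- Enter that variable, gastrointestinal bleeding and intracranial hemorrhage by recency before index, for example 0 to 30, 31 to 90, 91 to 365 days, and none. Merge cells that are sparse in one arm.
- State that these are measured for controls at their Aim 2 index date, and reconcile this with the July 1 anchor in Adjustment covariates.
- Report balance on the recency categories in Table 4.

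The cost is a few more score terms from claims already held, and a somewhat lower effective sample size where the arms overlap little in a recent-event cell. Recency terms leave the two index-date rules as they are, so the remaining difference in how the arms enter should be named as a limitation.
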